### 2.2. Study 2: Prevalence and Related Factors of Prolonged Grief Disorder of Bereavement in COVID-19

This study intends to longitudinally explore the characteristics of mental health and demographic and loss-related factors associated with prolonged grief symptoms among bereaved Chinese individuals during COVID-19 pandemic. The researchers are concerned with not only the level of grief reactions (between-individual differences) but also its change (within-individual differences). About 500 bereaved Chinese will be recruited online.

#### 2.2.1. Sample

Participants can be included in this study if they are over the age of 18 and have lost their first-degree relatives during COVID-19.

Exclusion criteria consists of a lifetime history of severe mental disorder (e.g., schizophrenia, bipolar disorder); intellectual disability; alcohol or substance abuse or dependence within the past six months; strong suicidal intention.

#### 2.2.2. Procedure

An online link will be sent to the participants who meet the inclusion criteria. Once the participants access the link, the information concerning the research purpose, and the informed consent form, will appear. Only when the participants select “I understand the above information and agree to participate in this research,” will they begin the formal study. At the end of the survey, the researcher will provide the participants with a supporting resource package (including hotline number, self-help resources, and related websites). Assessments will be conducted at two time points: baseline (T0) and six months after the baseline (T1).

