### 1.5. Rationale for the Research

In view of the urgency of mental health assistance for the bereaved during COVID-19, we set up a team and designed this present research. Notably, this research is not only a scientific research project, but also a social welfare project. Whether or not the bereaved research participants are willing to have their data collected for this research, we will provide free grief consulting services for more than 160 bereaved individuals during the research period.

The first aim of this project is to train and evaluate Chinese grief consultants with reference to the more developed western grief consultant training system, and to fill the huge gap of grief consulting in China. Secondly, previous studies suggest that related factors (such as unexpected death, social isolation, and multiple losses) may hinder the process of adaptation and recovery of bereaved individuals, but the mechanism remains to be elucidated, so it is necessary to design a longitudinal study to investigate the mental health and associated factors of the bereaved in China [31]. Finally, we set out to develop a grief counseling program suitable for Chinese culture to provide support for bereaved people during COVID-19, while verifying the effectiveness of the design, and supplementing grief research.

The principal research objectives are to:

Investigate demographic and related factors associated with prolonged grief symptoms among Chinese individuals bereaved due to COVID-19 (including grief reaction, trauma response, depression, anxiety, and suicide risk).Develop training and evaluation programs for Chinese professional grief counselors to develop and examine their competence.Provide grief counseling for the bereaved during the pandemic and assess the effect of the intervention.

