#### 2.2.3. Measures

In order to alleviate the discomfort that the bereaved may feel when filling in the questionnaires, the researchers will try to reduce the number of the items as much as possible. Table 1 shows all the measures that will be carried out at each time point.

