##### Primary Outcomes

Prolonged Grief Questionnaire (PG-13) [8] and Inventory of Traumatic Grief (ITG) [36] will be used to measure the grief symptoms of the bereaved. Post-traumatic stress symptoms will be assessed by the 20-item PTSD Checklist for DSM-5 (PCL-5) [37]. Depression Anxiety and Stress Scale (DASS-21) [38] will be used to measure the depressive symptoms, anxiety symptoms, and stress status of the bereaved. Posttraumatic Growth Inventory (PTGI) [39] will be used to assess the perceived benefits from traumatic events.

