##### Secondary Outcomes

The Scale for Suicidal Intention (SSI) [40] will be used to measure the severity of suicidal intentions. Maladaptive cognitions common in the bereaved will be measured by the Typical Beliefs Questionnaire (TBQ) [41]. The Grief-related Avoidance Questionnaire (GRAQ) [9] will be used to assess the avoidance behaviors of the bereaved. The Work and Social Adjustment Scale (WSAS) [42] will be used to assess the participants’ functioning in work, social adjustment, management, and family relationships.

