## 5. Ethics, Consent and Permissions

This research will follow the latest version of the Declaration of Helsinki. The study protocol was approved by the Institutional Ethics Committee of Beijing Normal University and the Chinese clinical trial registry has approved the study (Register ID: ChiCTR2000038255). Informed consent to participate in the study will be obtained from all participants. Participants will be informed that they can withdraw at any time from the study without consequences.

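### Study 2 hands over its support package at the end of the survey, so a participant who stops the baseline survey part-way may leave without it

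*Protocol article*

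**What the plan says.** Section 2.2.2 of the protocol article sets out the Study 2 survey in order. Eligible people are sent a link. "Once the participants access the link, the information concerning the research purpose, and the informed consent form, will appear". Those who select agreement then begin the formal study. Support comes last: "At the end of the survey, the researcher will provide the participants with a supporting resource package", described as "including hotline number, self-help resources, and related websites". The survey is run at baseline (T0) and once more at follow-up (T1).

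Four other places bear on this point:

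- Section 2.2.3 plans to keep the number of items low, and gives its reason: "In order to alleviate the discomfort that the bereaved may feel when filling in the questionnaires".
- The outcome sections and Table 1 show sensitive content. "Post-traumatic stress symptoms will be assessed by the 20-item PTSD Checklist for DSM-5 (PCL-5"), and a further scale "will be used to measure the severity of suicidal intentions".
- Section 5 states: "Participants will be informed that they can withdraw at any time from the study without consequences".
- Section 2.2.1 excludes, among others, people with strong suicidal intention.

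**The concern.** The one support step described for the survey itself comes after all the questionnaires. A person who finds the questions too distressing and closes the survey is among those the package is meant for. On the sequence as written, that person may not reach it.

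What is at stake is participant safety in a bereaved population that answers questions on grief, trauma and suicidal intention online. Sample size, analysis and interpretation are not involved.

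**Working it through.** No formula applies and the plan gives no figure to reproduce. The check is one of sequence: where the package is given, whether it is given anywhere else, and who can leave before that point.

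**1. Delivery point.** Section 2.2.2 gives five steps in order: link, information and consent form, agreement, formal study, package. The package is the last.

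**2. Any other delivery point.** None is described elsewhere in the article. The sentence on what appears when the link is opened names the research purpose and the consent form, and no support resources. Section 2.2.3 responds to discomfort by reducing items, which may make stopping less likely but gives nothing to a person who does stop. Section 1.5 promises that "we will provide free grief consulting services for more than 160 bereaved individuals during the research period", whether or not those people agree to data collection. It does not say that someone leaving the Study 2 survey is told of this.

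**3. Who can leave before the package.**

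| Participant | Scales seen before the package is given, on the described sequence |
|---|---|
| Declines consent | None |
| Consents and stops T0 part-way | Some, up to the full baseline set |
| Completes T0, then starts T1 | Package already given at the end of T0 |

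Only the middle row is exposed, so the point is confined to T0.

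**4. Is the middle row foreseeable?** Yes, from the article itself: discomfort is expected (section 2.2.3) and stopping is permitted (section 5).

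**5. How much could such a person have seen?** Table 1 marks nine named scales at baseline: PG-13, ITG, PCL-5, PTGI, DASS-21, TBQ, GRAQ, WSAS and SSI. Nine is a ceiling. The order of presentation is not given, so nothing shows that a person who stops has reached the PCL-5 or the suicidal-intention scale.

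**6. How many people?** The count would be about 500 recruits × the T0 break-off rate × the share of those leavers who get the package by no other route. The article gives neither of the last two factors, so no head-count is supported.

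**The case against.** The strongest reply is that this rests on a condensed article's description of a safeguard.

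- The text does not say that the package is given *only* at the end. It makes the researcher the giver and the participants, not the completers, the recipients. Since a link is sent to participants, there may be a contact route outside the questionnaire.
- The consent form is not reproduced and may already list support contacts.
- The exclusion of people with strong suicidal intention lowers the risk.
- Section 5 reports ethics committee approval.

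Most of this stands, and it limits the claim to *may leave without it* on the described sequence. It does not remove the point. The article does more than stay silent: it fixes a delivery point, and that point falls after the scales. The exclusion leaves in people with lesser distress, and suicidal intention is still measured in those who enter.

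A reader might infer more in three ways, none of which the article supports:

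- *That early leavers certainly receive nothing.* The article does not say so, and either the consent form or direct contact could already close the gap.
- *That a stated number of people would be affected.* Any assumed break-off rate would have no source in the article.
- *That the free counseling in section 1.5 can be counted as spare capacity for early leavers.* Study 3 itself enrols 160 people, so the promised places may largely be theirs.

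**Conclusion.** The point holds as a minor, optional improvement to participant safety. As section 2.2.2 is written, a consenting participant who stops the T0 survey part-way may miss the hotline and other resources, and the article itself gives reason to expect that some may stop.

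Its size cannot be put as a number. It concerns T0 only, and only those who consent and then stop. It rests on reading the end of the survey as the point after the last questionnaire, and on there being no further delivery route in the consent form, the survey build or a fuller protocol. If any of these already provides the package to early leavers, one clarifying sentence settles the matter. The article does not contradict itself here, and no estimate, error rate or sample size is affected.

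**What to change.** Amend section 2.2.2 so that the support package already planned is shown at three points:

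1. on the information and consent page, before the first scale;
2. on any early-exit page;
3. at the end of the survey, as now.

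The first is the most useful, because every participant sees that page and it does not depend on how a person leaves. If the consent form already lists these resources, stating so in section 2.2.2 is enough.

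The only downside is a small change to survey layout. The package and the opening page are both already planned, and no staff, visits, items or participants are added. No clinical threshold or treatment rule is needed.

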### 2.3. Study 3: Grief Counseling for Bereaved Chinese during COVID-19

Based on the above grief therapy description, combined with the results of study two, the researchers will develop an online grief counseling plan that is more suitable for Chinese culture. The counseling is expected to include 8–10 sessions (one hour per session). The themes of each of the sessions are: (1) understanding and accepting grief reactions; (2) managing painful emotions; (3) learning to care for yourself; (4) increasing contact with others; (5) coping with difficult days; and (6) adapting to a new life.

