#### 2.3.1. Sample

One-hundred-sixty bereaved Chinese will be recruited online. The inclusion criteria in study three are the same as study two.

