## 3. Statistics Analyses

IBM SPSS Version 25 (Armonk, New York, USA) will be used to analyze the data. Both completer analyses and intention-to-treat analyses (using the method of last observation carried forward) will be carried out. Descriptive characteristics of the sample will be calculated as obtained counts (*n*) and simple proportions (%), with missing items reported as missing.

For study one, the measurements at three different time points will be compared using the analyses of variance (ANOVA) for continuous variables and the chi-square test for categorical variables.

In addition, in study two, the researchers will employ linear regression analyses to examine the predictors of PG-13, DASS-21, PCL-5 and PTGI at each time point, while controlling for gender, age, education level, marital status, and religious beliefs. The cross-lagged model will be used to further clarify the direction of the relationship between the predictors and outcome variables. A *p*-value < 0.05 (2-tailed) will be taken to indicate statistical significance.

For study three, Chi-square tests and ANOVAs will be conducted on baseline scores to rule out significant differences between groups on demographic or loss-related or outcome variables before treatment. The treatment effects on the primary outcome variables will be examined with a 2 (groups) × 3 (time points) multivariate analysis of variance (MANOVA), with three time points (baseline, post-counseling, and three months follow-up) as the repeated measures. The outcomes of treatments will be further investigated separately with the analyses of covariance (ANCOVA), using baseline scores of the outcome variables as covariates.

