## Figures and Tables

**Figure 1 ijerph-18-09061-f001:**
[figure not shown]
Study design.

**Table 1 ijerph-18-09061-t001:** Schedule of assessments.

Measures	Baseline	Follow-Up (3 Months after Baseline)
Socio-demographic information	×	
PG-13	×	×
ITG	×	×
PCL-5	×	×
PTGI	×	×
DASS-21	×	×
TBQ	×	×
GRAQ	×	×
WSAS	×	×
SSI	×	×
Therapy expectations	×	×

PG-13 = Prolonged Grief Questionnaire; ITG = Inventory of Traumatic Grief; PCL-5 = PTSD Checklist for DSM-5; PTGI = Posttraumatic Growth Inventory; DASS-21 = Depression Anxiety and Stress Scale; TBQ = Typical Beliefs Questionnaire; GRAQ = Grief-related Avoidance Questionnaire; WSAS = Work and Social Adjustment Scale; SSI = the Scale for Suicidal Intention.

**Table 2 ijerph-18-09061-t002:** Schedule of assessments.

Measures	Baseline (Before Randomization)	Post-Counseling	Follow-Up (3 Months after the Post-Counseling)
Socio-demographic information	×		
PG-13	×	×	×
ITG	×	×	×
PCL-5	×	×	×
PTGI	×	×	×
DASS-21	×	×	×
TBQ	×	×	×
GRAQ	×	×	×
WSAS	×	×	×
SSI	×	×	×
Therapy expectations	×		

PG-13 = Prolonged Grief Questionnaire; ITG = Inventory of Traumatic Grief; PCL-5 = PTSD Checklist for DSM-5; PTGI = Posttraumatic Growth Inventory; DASS-21 = Depression Anxiety and Stress Scale; TBQ = Typical Beliefs Questionnaire; GRAQ = Grief-related Avoidance Questionnaire; WSAS = Work and Social Adjustment Scale; SSI = the Scale for Suicidal Intention.

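### Study 2 neither prevents nor records grief counseling between its two waves, so its change results may mix adaptation with treatment and this could not be checked

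*Protocol article*

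**What the plan says.** - **Aim and size of Study 2.** Section 2.2 states: "About 500 bereaved Chinese will be recruited online". It is interested in the level of grief "but also its change (within-individual differences").
- **Follow-up.** Section 2.2.2: "Assessments will be conducted at two time points: baseline (T0) and six months after the baseline (T1"). The heading of Table 1 reads differently: "Follow-Up (3 Months after Baseline").
- **Shared population.** Section 2.3.1: "The inclusion criteria in study three are the same as study two". Both studies recruit online.
- **Counseling on offer.** Section 1.5: "we will provide free grief consulting services for more than 160 bereaved individuals during the research period". This applies whether or not the recipients agree to give data.
- **Sequence.** Section 2.3: "combined with the results of study two, the researchers will develop an online grief counseling plan".
- **Measures.** Section 2.2.3 presents Table 1 as the full set of Study 2 measures. Table 1 has a therapy-expectations row ticked at both waves and no row for counseling or therapy received. In Table 2, for the counseling trial itself, therapy expectations are ticked at baseline only.
- **Analysis.** Section 3 plans linear regressions at each time point, "while controlling for gender, age, education level, marital status, and religious beliefs", and a cross-lagged model to establish direction. Neither has a term for counseling.

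**The concern.** A longitudinal study of how people adapt to loss has to know who was treated between its measurements. Here the same project supplies a treatment to people who meet the same criteria, and the article leaves open whether some of them are also Study 2 respondents with a second wave still to come.

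Uptake of counseling is unlikely to be random. Distress, avoidance, maladaptive beliefs and poor functioning, all measured at T0, plausibly prompt people to seek help, and effective help lowers grief at T1. A baseline factor that slows adaptation could then look weaker than it is, because the people who carry it were more often treated. Average change could look like natural recovery when part of it is treatment.

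The T1 regressions, the cross-lagged paths and the description of change are exposed to this. Baseline prevalence and the T0 regressions are not. If T1 is collected without a question on counseling received, project counseling might later be recovered by linking records, but counseling obtained elsewhere could not.

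**Working it through.** **The plan's own figure first.** The only calculated figure is the Study 3 sample size in section 2.3.2 (effect 0.5, α 0.05, power 0.80, dropout 20%). Two-sided testing is stated in section 3 in the Study 2 paragraph and assumed here for Study 3.
- Normal approximation: 63 per arm; 63/0.80 = 78.75, so 79 per arm and 158 in total.
- t-test: 64 per arm; 64/0.80 = 80 per arm and 160 in total.

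The stated 160 reproduces. It is not in dispute; it supplies the effect size used below.

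**Shift in mean Study 2 change.**

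Inputs from the article: N = 500 (section 2.2) and effect d = 0.5 (section 2.3.2).

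Assumptions: k, the number counseled before T1; r, the correlation between waves, 0.5 to 0.7; equal SDs at both waves; no dropout; d = 0.5 carries over to Study 2 respondents.

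- Shift = (k/500) × 0.5 SD.
- Standard error of mean change = √(2(1 − r)/500). For r = 0.5 this is √(1/500) = 0.045 SD; for r = 0.7 it is √(0.6/500) = 0.035 SD.

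| Counseled before T1 (k) | Share of 500 | Shift (SD) | Shift in standard errors (r = 0.5 to 0.7) |
|---|---|---|---|
| 0 | 0% | 0 | 0 |
| 20 | 4% | 0.02 | 0.45 to 0.58 |
| 40 | 8% | 0.04 | 0.89 to 1.15 |
| 80 | 16% | 0.08 | 1.79 to 2.31 |
| 160 | 32% | 0.16 | 3.58 to 4.62 |

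**How plausible the rows are.** The row at 80 already takes a full counseling arm from the Study 2 cohort and treats it before T1. The row at 160, if filled from the trial, also needs the waitlist arm treated before T1, yet that arm is the control up to T2, three months after counseling ends. If sessions were weekly (an assumption), 8 to 10 weeks plus three months is about five months. That leaves roughly one month of a six-month window and nothing of a three-month one. Section 1.5 speaks of more than 160 recipients, so others may be counseled, but nothing places them in the Study 2 cohort.

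**Shift in a regression coefficient.** Study 2 mainly reports coefficients, so the mean shift is only part of the picture. For a standardized predictor, leaving out counseling changes its coefficient by about 0.5 × ρ × √(p(1 − p)), where ρ is the correlation of predictor with uptake and p the share counseled. With ρ = 0.3 (assumed):
- p = 8%: 0.5 × 0.3 × 0.271 = 0.041 SD
- p = 16%: 0.5 × 0.3 × 0.367 = 0.055 SD
- p = 32%: 0.5 × 0.3 × 0.466 = 0.070 SD

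It is zero if uptake is unrelated to the predictor, and larger if ρ is larger.

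**The case against.** A reader might infer that Study 2's change scores are in fact contaminated by the project's own treatment. The article does not support that. It states no overlap between the cohorts. Study 2 respondents are given a hotline number, self-help material and websites, with no stated referral to Study 3. Section 2.3 builds the counseling plan partly on Study 2 results, which points to at least partial sequencing. It does not say whether baseline results or both waves are meant, so this makes overlap less likely without excluding it. Even strict sequencing would leave help from elsewhere, including help reached through the resource package, unrecorded.

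It can also be said that a condensed article may leave a treatment-received item to the full protocol. That has some force: section 2.2.3 says loss-related information is collected, and Table 1 has no separate row for it, so the table is not complete to the last item. Against this, the article itself presents Table 1 as the complete list, aims to keep the item count low, and spends a follow-up item on expecting therapy. That row may simply have been carried over from Table 2, and it is no evidence that Study 2 respondents enter therapy.

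One might want uncounseled respondents as the main analysis. That objection to the simplest remedy stands: counseling arises after baseline, depends on distress and is partly a consequence of the T0 factors under study. Restricting to the uncounseled would drop the more distressed and introduce selection bias.

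**Conclusion.** The point holds in conditional form. Study 2 neither prevents nor records counseling between its waves, while it shares its eligible population with a trial in a project that gives counseling free. Its change and cross-lagged results may mix adaptation with treatment, and the planned data could not show whether they do.

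The size depends on an unstated overlap. It is nil without counseling between waves, and 0.04 to 0.08 SD in mean change for 40 to 80 counseled, which is about one to two standard errors. The 0.16 SD figure is not a realistic expectation. These figures rest on the planned effect of 0.5 applying in this cohort and on the assumed between-wave correlation; those for coefficients rest also on an assumed link between predictor and uptake. This is a worthwhile improvement at almost no cost, and it does not show that Study 2 is invalid.

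**What to change.** 1. In Table 1, at the Study 2 follow-up only, replace the therapy-expectations item with one on grief counseling or therapy received since baseline: yes or no, number of sessions, and whether in this project or elsewhere.
2. Link Study 2 and Study 3 identifiers, with consent that covers the link, and state the order of the two studies and whether Study 2 respondents may enter Study 3 before T1.
3. Keep all respondents as the main analysis. As sensitivity analyses, repeat the T1 regressions and the cross-lagged model (a) with counseling received as a covariate and (b) in uncounseled respondents. State that both condition on a post-baseline variable, so neither is a clean estimate of untreated adaptation.
4. Reconcile the follow-up interval between section 2.2.2 and the abstract (six months) and Table 1 (three months).

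The cost is one item exchanged for another, so respondent burden stays about the same, plus an identifier link and one or two extra models. Therapy expectations at the Study 2 follow-up would be lost; no planned analysis in section 3 uses them.
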